#### Strategies to improve adherence to interventions {11c}

To improve adherence to medication by calculating the number of remaining doses based on the medication records in the patient logbook.

#### Relevant concomitant care permitted or prohibited during the trial {11d}

Since relugolix is a substrate of p-glycoprotein, concomitant use of erythromycin, which inhibits p-glycoprotein, or rifampicin, which induces p-glycoprotein, increases or decreases the blood concentration of relugolix, so these drugs will be restricted to concomitant use during the study period. Patients will be carefully monitored for adverse reactions to the study drug by interview and examination, and the study drug will be continued under supportive care. Supportive care includes antidepressants for depression, hepatotropic agents (ursodeoxycholic acid or stronger neo-minophagen C) for abnormal liver function, oral hemostatic agents (carbazochrome sodium sulfonate hydrate and tranexamic acid) for irregular vaginal bleeding, and iron intravenous and oral administration of iron for iron deficiency anemia associated with illicit genital bleeding are acceptable.

#### Provisions for post-trial care {30}

The post-trial care is planned to conduct myomectomy (laparotomy, laparoscopically, or hysteroscopically) or total hysterectomy (laparotomy or laparoscopically). The post-treatment is performed within 1 week after completion of 24 weeks of study drug administration. In the unlikely event that the time between the end of the study and this post-treatment is extended, patients will receive relugolix continuously during the period.

### Outcomes {12}

The primary endpoint will be the reduction of leiomyoma volume before and after the administration of relugolix. The secondary endpoints will be the reduction (%) of uterine volume compared with pre-treatment, change (score) of total Kupperman Index score at 24 weeks compared with pre-treatment, change rate (%) of bone mineral density (BMD) at 24 weeks compared with the baseline, and change rate (%) of bone metabolism markers(serum BAP) at 24 weeks compared with the baseline. The investigative assessments will be the total number of days of genital bleeding and the change in gonadotropic and sex hormone levels such as luteinizing hormone (LH), follicle-stimulating hormone (FSH), estradiol (E2), and progesterone (P4) at 24 weeks compared with the baseline. The MRI scans will be outsourced to another hospital, and tumor and uterine volume will be evaluated by the radiologist in the hospital with blind.

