### Objectives {7}

This trial aims to prove the non-inferiority of leiomyoma reduction effect and safety evaluation (i.e., reduction of side effects) by every-other-day administration for 16 weeks after 8 weeks of everyday administration compared to throughout the duration.

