#### Intervention description {11a}

The initial dose of relugolix is 40 mg orally once daily before meals, starting on days 1–5 of the menstrual cycle until day 56. On day 57, the control group will continue taking 40 mg of relugolix every day, and the intervention group will switch to 40 mg of relugolix every other day. However, change to another group will not be permitted.

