#### Participant timeline {13}

Eligible participants who are referred to our hospital will be recruited. Participants will be asked to complete an informed consent form by an on-site researcher if they choose to participate in the study (Fig. 1). They will complete the baseline assessments and will be randomly assigned to the intervention or control group. All patients will have follow-up visits monthly, and all outcome data will be collected by research assistants (Table 1).

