### Data collection and management

#### Plans for assessment and collection of outcomes {18a}

Eligible participants will be invited to complete questionnaires, physical measurements, vital signs, imaging, laboratory, and bone mineral density testing as a baseline before randomization. The regular items of vital signs, body weight, PS, and the existence of adverse effects will be verified monthly after the beginning of the study. Before the administration, 8 weeks, and after 24 weeks of relugolix administration, laboratory tests, ultrasound examinations, and questionnaires will be conducted in addition to the monthly regular items. Additional examinations including laboratory tests or ultrasound examinations will be conducted in case the attending physician determined it necessary. Questionnaires include the number of days with abnormal genital bleeding and the Kupperman Index. Kupperman Index covers 11 menopausal symptoms including hot flushes (vasomotor), paresthesia, insomnia, nervousness, melancholia, vertigo, weakness, arthralgia or myalgia, headache, palpitations, and formication. Each symptom is rated on a scale from 0 to 3 for having no, slight, moderate, or severe complaints, respectively, with the highest possible total score being 51. Imaging will be admitted by magnetic resonance imaging (MRI) examination, by which select the leiomyoma with the longest diameter (excluding a calcified leiomyoma), measure in three directions in a metric system (vertical and horizontal lengths by coronal section and anteroposterior diameter by sagittal section), and calculate the volume (D1 × D2 × D3 × *π*/6) from the 3 diameters (D1, D2, and D3). Pelvic MRI scans just after the completion of the relugolix administration are acceptable with a timing error of ± 1 week. For abnormal genital bleeding, the total number of days of bleeding will be recorded using a patient diary.

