## Statistical methods

### Statistical methods for primary and secondary outcomes {20a}

The assessment of primary endpoint will be assessed as follows: we defined the null hypothesis as “The mean rate of change in the intervention group is more than 20% inferior to the mean rate of change in the control group,” and this will be tested with a one-sided *t*-test at a significance level of 2.5%. In addition, 95% confidence intervals for the mean rate of change are calculated for each group and for the difference between the groups. The assessment of the secondary endpoint will be analyzed as follows. (1) Change in uterine volume from before study drug administration at 24 weeks after study drug administration (%). The measured values before the start of treatment and at 24 weeks and the rate of change at 24 weeks will be summarized for each group using descriptive statistics. The 95% confidence interval of the difference between the groups will be calculated for the mean of the rate of change. (2) Change in the total score of the Kupperman Index from before the study drug administration at 24 weeks after the study drug administration (points). (3) Percent change in bone mineral density (BMD) from baseline at 24 weeks post-treatment (%). The measurements before and at week 24 of treatment and the percent change at week 24 of treatment will be summarized for each group by descriptive statistics. In addition, the null hypothesis “the mean rate of change for the intervention group is equal to the mean rate of change for the control group” will be tested with a two-sided 5% *t*-test at the significance level. In addition, 95% confidence intervals for the mean rate of change will be calculated for each group and for the difference between the groups. (4) Percentage change in bone metabolism markers (serum BAP) at 24 weeks after treatment compared to before treatment with the study drug (%). The measured values before the treatment and at 8 and 24 weeks of treatment, and the change (%) at 8 and 24 weeks of treatment will be summarized for each group using descriptive statistics, and a graph of the mean ± standard deviation will be prepared for each time point. The null hypothesis “the mean of the amount (rate) of change in the intervention group is equal to the mean of the amount (rate) of change in the control group” is tested with a two-tailed *t*-test at a significance level of 5%. In addition, 95% confidence intervals for the mean of the amount (rate) of change will be calculated for each group and for the difference between the groups. Data for each endpoint will be analyzed after the period for collecting the data has ended and the data have been fixed. The intermediate analysis will not be performed.

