## Discussion

There is no proceeding trial, at least to our knowledge, that investigated into size reduction effect by every other day administration of relugolix. The Osuga et al. [18] phase III trial aimed to compare the effectiveness of relugolix 40 mg/day with leuprorelin 1.88 or 3.75 mg monthly injections in treating uterine leiomyoma patients over 24 weeks. The trial found that daily administration of relugolix 40 mg/day significantly reduced tumor volume by 41% at 12 weeks. Thereafter, the tumor volume appeared to stabilize at 24 weeks with a 49% reduction compared to the baseline. This suggests that the volume reduction effect of leiomyoma through everyday administration of relugolix is likely to reach a plateau at 12 weeks. Adverse effects of climacteric disorder induced by relugolix administration in clinical settings occur around 8 weeks after the start of treatment. In the current trial, we expect that daily administration of up to 8 weeks, by which climacteric disorder symptoms are less likely to occur, followed by a change to every other day administration, would escape complications while maintaining the effect of leiomyoma volume reduction. Relugolix has a longer half-life, allowing for once-daily administration and improving patients’ compliance with long-term therapy [19, 20]. It may also be suitable for every other day administration.

The relugolix combination therapy is a once-daily treatment for uterine myomas or endometriosis. It comprises 40 mg relugolix, 1 mg estradiol, and 0–5 mg norethisterone acetate. The therapy helps maintain hormone base levels at about the early follicular phase concentration of the menstrual cycle, which reduces vasomotor symptoms and minimizes bone density loss. Several randomized third-tier trials have been conducted to test the effectiveness of the therapy [15, 21–23]. In the LIBERTY study, which focused specifically on myomas, both the relugolix combination and the delayed group showed significant improvements in menstrual volume, pain, bleeding distress, pelvic discomfort, anemia, and uterine volume when compared with the placebo group [15]. However, neither the relugolix combination nor the delayed group showed any significant reduction in maximum uterine myoma volume. The above trial may not be sufficient for reducing myoma volume before less invasive surgery. However, the current trial has the potential to advocate new methods of administering these combination therapies.

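### The Kupperman endpoint rests on one score at week 24, so graded climacteric symptoms are not compared over the 16 weeks in which the regimens differ, and the raw change score gives up precision

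*Protocol article*

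**What the plan says.** All references are to the protocol article.

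- **Aim.** Objectives {7} sets out a "safety evaluation (i.e., reduction of side effects) by every-other-day administration for 16 weeks after 8 weeks of everyday administration". The abstract's Discussion paragraph and the conclusion of the main Discussion speak of superiority on this side of the trial.
- **Rationale.** The Discussion says: "Adverse effects of climacteric disorder induced by relugolix administration in clinical settings occur around 8 weeks after the start of treatment". It expects a change of regimen at that point to avoid the symptoms.
- **When the arms separate.** Intervention description {11a}: "On day 57, the control group will continue taking 40 mg of relugolix every day, and the intervention group will switch". Treatment is the same in both arms before that.
- **Endpoint.** Outcomes {12} lists the "change (score) of total Kupperman Index score at 24 weeks compared with pre-treatment". Statistical methods {20a} repeats this contrast as item (2), with no analysis text directly attached to it.
- **Collection.** Plans for assessment and collection of outcomes {18a}: "Before the administration, 8 weeks, and after 24 weeks of relugolix administration, laboratory tests, ultrasound examinations, and questionnaires will be conducted". It adds: "Questionnaires include the number of days with abnormal genital bleeding and the Kupperman Index".
- **Visits.** Participant timeline {13}: "All patients will have follow-up visits monthly". Section {18a} has adverse effects verified at these visits.
- **Abstract.** Its Methods paragraph lists climacteric disorder among the secondary endpoints as something that occurs or does not. Outcomes {12} and Statistical methods {20a} carry only the week-24 score change.

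**The concern.** The tolerability question is what happens to climacteric symptoms from day 57 to week 24. The planned comparison takes one reading at the end of that period and subtracts a reading made 24 weeks earlier. A difference between the arms at weeks 12, 16 or 20 that had narrowed by week 24 would not appear in the only graded symptom endpoint. The monthly adverse-effect checks do not fill this gap as written: no between-arm comparison of climacteric events is stated, and the safety endpoints in Adverse event reporting and harms {22} are depression, hepatic dysfunction, angina and severe anemia.

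The second issue is precision. A raw change score carries the full noise of the pre-treatment reading. Adjusting the week-24 score for that reading uses the same data and is at least as precise when the SD is the same at both visits.

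At stake is how well the trial can answer the second half of its aim. Scores not collected at weeks 12 to 20 cannot be recovered by later analysis wording.

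**Working it through.** **Coverage.** Scheduled Kupperman scores: pre-treatment, week 8, week 24. The arms diverge on day 57, so one of the three scores is post-switch, and no score is scheduled between week 8 and week 24, an interval of 24 − 8 = 16 weeks. If monthly means four-weekly, post-switch visits fall at about weeks 12, 16, 20 and 24, and three of the four carry no Kupperman score.

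**Sample size used.** The article sizes the trial on the primary endpoint only. With a true difference of 41 − 36 = 5 points, margin 20, SD 30, one-sided 2.5% and 80% power, the normal formula gives 2 × 30² × (1.960 + 0.842)² / (20 − 5)² = 62.8, so 63 per group. With the t-test, power is 0.795 at 63 and 0.801 at 64, so the stated 64 reproduces. I use 64 per arm below. No figure is stated for the Kupperman Index.

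**Precision: an illustration on assumed inputs.** The article gives no Kupperman SD, correlation or target difference. I assume the same SD at every visit, the same correlation r between any two visits, a two-sided 5% level and 80% power. Variances are in units of SD²:

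- A. Raw change, pre-treatment to week 24: 2(1 − r)
- B. Week 24 adjusted for pre-treatment: 1 − r²
- C. Mean of weeks 12, 16, 20 and 24 adjusted for pre-treatment: (1 + 3r)/4 − r²

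Detectable difference = 2.80 × √(2 × variance / 64).

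At r = 0.6:

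- A: 2 × 0.4 = 0.80; 2.80 × √0.0250 = 0.44 SD
- B: 1 − 0.36 = 0.64; 2.80 × √0.0200 = 0.40 SD
- C: 0.70 − 0.36 = 0.34; 2.80 × √0.0106 = 0.29 SD

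| r | A: planned | B: week 24 adjusted | C: weeks 12–24 mean adjusted |
|---|---|---|---|
| 0.4 | 0.54 | 0.45 | 0.31 |
| 0.6 | 0.44 | 0.40 | 0.29 |
| 0.7 | 0.38 | 0.35 | 0.26 |

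The ratio of B to A in variance is (1 − r²) / [2(1 − r)] = (1 + r)/2. It is below 1 for every r below 1, and is 0.80 at r = 0.6. Under equal SDs, adjustment therefore never loses precision.

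**How far C depends on the shape of the effect.** C is directly comparable with A and B only if the difference is constant from week 12. Suppose instead that it builds linearly: 0.25, 0.50, 0.75 and 1.00 of its week-24 size at weeks 12, 16, 20 and 24. The mean is 2.50/4 = 0.625 of the week-24 effect. At r = 0.6, C then corresponds to 0.29/0.625 = 0.46 SD in week-24 terms, no better than A (0.44) and worse than B (0.40).

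**The case against.** Several stronger readings are tempting, and the article does not support them.

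- **That symptoms after week 8 go unobserved.** They do not. Adverse effects are verified monthly, section {11d} describes monitoring by interview and examination, and bleeding is kept in a diary. What is missing is a graded score between weeks 8 and 24 and a stated between-arm comparison.
- **That the week-8 score is unused.** This is not established. The week-8 summaries in {20a} stand under serum BAP, but that text refers to an amount as well as a rate of change, and may have been meant to cover the Kupperman score in points. The analysis plan is not shown, and descriptive summaries are commonly left to it.
- **That a real benefit is likely to be missed.** Without an SD, a correlation or an expected difference, a detectable difference of 0.44 SD does not show this. A woman who has adapted by week 24 is hypothetical: nothing in the article says that symptoms fade under continued dosing.
- **That the comparison is biased.** It is not. Randomization precedes treatment and the first 8 weeks are common to both arms, so the week-24 contrast is legitimate. It also matches the timing of BMD and BAP.
- **That the week-8 score should be a main covariate.** Adding it would lower the week-24 figure at r = 0.6 to 0.37 SD (variance 1 − 2 × 0.36/1.6 = 0.55). But it is a self-report collected after open-label randomization, from women who may know that they are about to switch, and expectation could affect it.

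It can also be said that this is a secondary endpoint and that more frequent scoring is a design preference. The first is true. Still, this is the only graded symptom measure of a stated aim, and the endpoint and the collection schedule are fixed in this article rather than left to an analysis plan.

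**Conclusion.** The point holds as one of coverage and precision. The tolerability aim covers 16 weeks, but the only graded symptom endpoint uses one reading at their end, and the abstract's occurrence endpoint has no counterpart in Outcomes {12} or the statistical methods.

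The gain from adjusting for the pre-treatment score is modest but needs no new data: 0.44 to 0.40 SD at r = 0.6. The larger gain from averaging, to 0.29 SD, requires a constant difference from week 12. Under a linear build-up the averaged score widens coverage and adds no power. All of these figures rest on assumed equal SDs and equal correlations, since the article gives neither.

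**What to change.** 1. Compare the week-24 Kupperman score between arms adjusted for the pre-treatment score, in place of the raw change.
2. Give the index at the existing visits around weeks 12, 16 and 20. Add a between-arm comparison of the mean score over weeks 12 to 24, adjusted for the pre-treatment score, and report the week-24 result alongside it.
3. Use adjustment for the week-8 score only as a sensitivity analysis.
4. Reconcile the endpoint with the abstract: either define how occurrence of climacteric disorder is counted and compared, or align the abstract with the score endpoint.

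The cost is a few minutes for an 11-item questionnaire at three visits that already take place, and a protocol amendment with review board approval and revised patient documents, as section {25} requires. If extra scores can no longer be collected, items 1, 3 and 4 need only changes of wording.

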**Discussion:**

This study aims to prove both the non-inferiority in leiomyoma volume reduction and superiority in adverse effects occurrence reduction, which will provide a novel method to escape adverse effects while maintaining the effect of leiomyoma reduction.

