## Introduction

### Background and rationale {6a}

Uterine leiomyomas are commonly detected with a prevalence reaching up to 60% of reproductive-aged women [1, 2] and affect women’s quality of life due to heavy menstrual bleeding or dysmenorrhea [3–5]. Leiomyomas grow according to estradiol exposure and decrease after post-menopause [6, 7]. In clinical practice, pharmacotherapy or surgical treatment is proposed for serious symptoms like abdominal distension, dysuria, infertility, or severe anemia due to heavy menstrual bleeding caused by leiomyomas. In the case of pharmacotherapy, a gonadotropin-releasing hormone (GnRH) receptor agonist (i.e., leuprorelin acetate or goserelin acetate) has been used to pause the menstrual cycle [8]. However, it induces a transient increase in gonadotropins and sex hormones, resulting in a clinical flare-up or temporary worsening of symptoms, and typically takes about 4 weeks to achieve a therapeutic effect [3, 9]. GnRH receptor antagonists (i.e., relugolix, elagolix, or linzagolix) are also used as newer treatments for uterine leiomyomas [10, 11]. Relugolix is a new orally active small molecule GnRH receptor antagonist [12–14] which proved its sufficient efficacy to suppress estradiol without the transient estradiol flare-up compared with GnRH agonist [15, 16]. However long-term administration should not be permitted liable to for climacteric disorder or osteoporosis. In the case of surgical treatment, pharmacotherapies like GnRH agonists or antagonists aimed at the reduction of leiomyoma and uterine volume or improvement of anemia are also introduced before the surgical treatment to conduct less invasive surgery (i.e., to reduce blood loss or surgical duration). However, the clinician often encounters cases in which menopausal symptoms are thought to be drug-related at about 8 weeks after the beginning of treatment, making it difficult to continue treatment [17]. Since the phase III trial was designed for relugolix administration to patients with leiomyoma, the leiomyoma volume as a secondary endpoint was reduced by 43.28 ± 33.85% by 12 weeks and 49.75 ± 34.33% by 24 weeks of administration compared with the baseline; we have hypothesized that everyday administration for 8 weeks and subsequently every-other-day administration of relugolix only for maintaining the effect could be a compatible method [18].

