#### Criteria for discontinuing or modifying allocated interventions {11b}

The criteria for discontinuing are as follows: (1) If the subject declines to participate in the study or withdraws consent; (2) If the subject is found to be ineligible after enrollment; (3) If the primary illness is completely cured by emergency surgery or other means and there is no longer a need for continued administration; (4) If the subject has persistent heavy genital bleeding due to deterioration of the primary illness and anemia of grade 3 or higher as defined in CTCAE v5.0 Grade; (5) The following serious adverse reactions associated with study drug administration are observed. Depression: when the patient does not respond to psychiatric treatment and the main cause is considered to be the study drug. Hepatic dysfunction: AST/ALT levels of grade 2 or higher in the CTCAE v5.0 Grade definition. Angina pectoris: diagnosed during the period of study drug administration; (6) Exacerbation of side effects associated with study drug administration that makes continuation of study drug administration inadvisable; (7) If the subject develops hypersensitivity to the study drug itself; (8) If the subject becomes pregnant; (9) If the subject’s medication adherence is extremely poor or over (< 70% of the total scheduled doses or > 120% of the total scheduled doses); (10) The subject fails to come to the hospital due to relocation or other reasons and is unable to receive relugolix for more than 8 weeks; (11) The entire study is terminated; (12) The physician deems it appropriate to terminate the subject’s continued participation in the study for other reasons; and (13) If the subject has any of the following serious adverse reactions to the study drug.

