#### Sample size {14}

Considering the results of leiomyoma volume reduction rate after the 12 weeks of continuous administration of 20 mg and 40 mg relugolix [19], we assume a change from baseline as − 41% and − 36% for the daily and every other day groups, respectively, and a common standard deviation (SD) as 30%. Set the non-inferiority margin as 20%, the significance level as 2.5% (one-sided), and the power as 0.8; the sample size requires a minimum of 64 patients in each group. Considering a dropout rate of approximately 10%, the total number of patients in this trial will be set at 70 patients in each group, for a total of 140 patients.

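### The Kupperman endpoint is scored at week 24, but the article schedules no score at a treatment stop, so a patient who stops for symptoms after the day-57 switch has no post-switch on-treatment value

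*Protocol article*

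**What the plan says.** Outcomes {12} lists four secondary endpoints. One of them scores climacteric symptoms: "change (score) of total Kupperman Index score at 24 weeks compared with pre-treatment". Statistical methods {20a} repeats it as item (2): "Change in the total score of the Kupperman Index from before the study drug administration at 24 weeks".

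The abstract's discussion makes tolerability a stated aim next to non-inferiority: "superiority in adverse effects occurrence reduction". The conclusion of the main Discussion also rests on superiority of the secondary endpoints.

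Plans for assessment {18a} fixes when the questionnaire is given: "Before the administration, 8 weeks, and after 24 weeks of relugolix administration, laboratory tests, ultrasound examinations, and questionnaires will be conducted". The monthly visits cover vital signs, weight, performance status and adverse effects. The extra examinations a physician may order are laboratory tests and ultrasound.

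Both arms take the same daily regimen to day 56 and separate on the next day: "On day 57, the control group will continue taking 40 mg of relugolix every day" (Intervention description {11a}), while the intervention arm switches.

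Stopping for side effects is foreseen. Discontinuation criterion (6) in section {11b} reads "Exacerbation of side effects associated with study drug administration that makes continuation of study drug administration inadvisable". The Background {6a} describes cases in which "menopausal symptoms are thought to be drug-related at about 8 weeks after the beginning of treatment, making it difficult to continue treatment".

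Section {20c}, headed for non-adherence and missing data, only repeats discontinuation criteria. Sample size {14} allows for loss in one phrase, "Considering a dropout rate of approximately 10" (per cent), not split by arm or reason.

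**The concern.** The endpoint is a score at one late time point, and the symptom it measures can itself make a patient stop before that time. Take a patient who stops at week 12 with severe hot flushes. Her last scheduled score is week 8, before the arms differ. Her week-24 score is either missing or taken about 12 weeks after the last dose, when drug-related symptoms may have eased. In both cases the event the endpoint should capture enters as nothing or as something mild.

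This is more than a matter of imputation wording that an analysis plan could supply later. A score that was never collected cannot be recovered. Carrying the week-8 score forward would not help, because at week 8 both arms have had the same treatment and the value holds no contrast between regimens.

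At stake is the tolerability half of the trial's claim. If the hypothesis is right and daily dosing produces more climacteric symptoms after the switch, the control arm loses more high scores and the comparison moves toward no difference.

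**Working it through.** **1. Timeline, from {11a} and {18a}**

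| Time | Kupperman scheduled in the text | Regimens |
|---|---|---|
| Baseline | yes | none yet |
| Week 8 (day 56) | yes | identical |
| Day 57 onward, monthly visits | no | different |
| After 24 weeks of administration | yes | different |

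The only scheduled score that reflects the allocated regimens is the last one. A patient who stops between day 57 and week 24 has no on-treatment score after the switch.

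**2. The plan's own figure.** The article gives no sample size for the Kupperman endpoint. For the primary test the inputs are margin 20, assumed difference 41 − 36 = 5, SD 30, one-sided 2.5%, power 0.8:

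n = 2 × (1.960 + 0.842)² × 30² / (20 − 5)² = 62.8, so 63 per group.

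With the noncentral t distribution, power is 0.795 at 63 and 0.8015 at 64. The stated 64 reproduces and the sample size is not in question. The same calculation shows that 64 per arm gives power of about 0.80 for any standardised difference of 15/30 = 0.5 SD in a two-sided 5% t-test. That is the reference used below.

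**3. Illustration.** Assumed, not in the documents: normal Kupperman changes with SD 1, true benefit 0.5 SD, 70 per arm, one common symptom threshold for stopping, and correlation ρ between the burden that triggers a stop and the week-24 score. The 10% stopping rate in controls borrows the plan's all-cause dropout figure. I read the two-sided 5% t-test printed after item (3) in {20a} as covering item (2) as well.

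- Control threshold: c = 1.2816, so 10% stop.
- Intervention, in its own SD units: 1.2816 + 0.5 = 1.7816, so 3.7% stop.
- Removing the stoppers lowers an arm's mean by ρ × φ(c)/Φ(c). Control: 0.1755/0.900 = 0.195. Intervention: 0.0816/0.9626 = 0.085.
- Observed benefit = 0.5 − ρ × (0.195 − 0.085) = 0.5 − 0.110ρ. This is 0.390 at ρ = 1 and 0.445 at ρ = 0.5.
- Completers: 70 × 0.90 = 63 and 70 × 0.963 = 67.4. With the correspondingly reduced variances, power is 0.71 at ρ = 1 and 0.74 at ρ = 0.5.
- References: 0.84 with all 70 per arm, 0.80 with the planned 64 completers.

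**4. How far the direction depends on who stops.** Separate simulation, 4,000 runs per row and column, 70 per arm, completers only. Assumed true benefit 4 points and SD 8. Cells give the mean estimate in points, with power in brackets.

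| Stopping, control / intervention | ρ = 0 | ρ = 0.5 | ρ = 1 |
|---|---|---|---|
| 10% / 10% | 4.01 (0.802) | 4.00 (0.821) | 4.04 (0.911) |
| 10% / 5% | 4.01 (0.803) | 3.64 (0.755) | 3.29 (0.759) |
| 15% / 5% | 4.00 (0.791) | 3.34 (0.666) | 2.67 (0.577) |
| 20% / 5% | 3.99 (0.776) | 3.03 (0.576) | 2.09 (0.398) |
| 5% / 10% | 4.02 (0.812) | 4.35 (0.885) | 4.67 (0.963) |

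Bias needs two things together: stopping related to the score, and different stopping rates in the two arms. Its sign follows the arm that stops more.

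**5. If off-drug week-24 scores are collected.** These patients stay in the comparison, but their scores may reflect recovery. The difference is again diluted if more of them are in the daily arm. The size depends on the degree of recovery, on which the article gives no figure.

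**The case against.** The strongest reply is that this is a condensed article. It refers to a statistical analysis plan and to a full protocol available on request, and the schedule table is not visible, so a discontinuation-visit questionnaire may exist there. That stands for imputation rules and analysis sets, and no fault is found with their absence. It does not remove the point about what the article does fix: a week-24 endpoint, and three questionnaire times of which none after the switch precedes week 24.

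Several stronger readings are tempting and the document does not support them:

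- A reader might take the Kupperman score to be the main tolerability endpoint. The article lists it as one of four secondary endpoints and gives it no such rank.
- A reader might infer that the worst outcomes will drop out of the comparison. No section says the analysis is limited to completers or that data collection ends when drug is stopped.
- A reader might state that the benefit will be understated. That requires more symptom-driven stops in the daily arm, which the Discussion's hypothesis implies but nothing shows. The Background's remark concerns about week 8, when both arms have had the same regimen, so stops before the switch should be balanced. Section {11d} also says drug is continued under supportive care, so stopping is not the routine response to symptoms.
- A reader might use the 10% dropout as a rate of symptom-driven stops in controls. It is an all-cause allowance.
- A reader might attribute the whole fall from 0.84 to 0.71–0.74 to bias. The part from 0.84 to 0.80 is loss of patients that the plan already allows for.

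Adverse effects are also recorded monthly, so a severe symptom leading to a stop remains in the safety data, though not in the endpoint.

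**Conclusion.** The concern holds in a conditional form. As the article's text stands, a patient who stops for worsening side effects after day 57 has no post-switch on-treatment Kupperman score, and any week-24 score is absent or off drug. If such stops are more frequent in the daily arm, a comparison of available week-24 scores is biased toward no difference.

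Under the step 3 assumptions, the loss is 0.055 to 0.11 SD of a true 0.5 SD. Power is 6 to 9 percentage points below the planned 0.80. The benefit, SD, stopping rates and correlation are all assumed, and a wider imbalance in stopping gives a larger loss.

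Severity is low to moderate. The endpoint is secondary and the trial was not sized on it, but it supports a stated aim, and the missing score cannot be recovered afterwards.

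**What to change.** In Plans for assessment {18a}: add the Kupperman questionnaire at the visit where study drug is stopped. Also collect it at week 24 regardless of treatment where possible, before surgery.

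In Statistical methods {20a}: keep the week-24 comparison as the endpoint analysis. Add one prespecified sensitivity analysis, limited to patients who stop because of climacteric symptoms. It would use their on-treatment score at the stop, or give them the worst rank and compare the arms with a Wilcoxon rank-sum test. Do not extend the worst rank to every drug-related stop: a patient stopped for raised AST/ALT or angina would then count as worst on climacteric symptoms. Report stops by arm and reason, so that readers can see which row of the step 4 table the trial resembles.

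The on-treatment stop score should not replace the main analysis. It mixes assessment times and depends on a stopping decision made open-label, which could favour the new regimen.

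Cost: one short existing questionnaire at a visit that already takes place, a week-24 contact for those who have stopped, and a few lines of protocol and analysis-plan wording. The criteria for stopping treatment are untouched.
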